## Abstract

**Background:**

The optimization of preventive strategies in patients at high risk of cardiovascular events and the evaluation of bottlenecks and limitations of transferring current guidelines to the real world of clinical practice are important limiting steps to cardiovascular prevention. Treatment with n-3 polyunsaturated fatty acids improves prognosis after myocardial infarction, but evidence of this benefit is lacking in patients at high cardiovascular risk, but without a history of myocardial infarction.

**Methods/design:**

Patients were eligible if their general practitioner (GP) considered them at high cardiovascular risk because of a cardiovascular disease other than myocardial infarction, or multiple risk factors (at least four major risk factors in non-diabetic patients and one in diabetics).

Patients were randomly allocated to treatment with n-3 polyunsaturated fatty acids (1 g daily) or placebo in a double-blind study and followed up for five years by their GPs to assess the efficacy of the treatment in preventing cardiovascular mortality (including sudden death) and hospitalization for cardiovascular reasons. The secondary, epidemiological, aim of the study is to assess whether it is feasible to adopt current guidelines in everyday clinical practice, with a view to optimizing all the available preventive strategies in people at high cardiovascular risk.

A nation-wide network of 860 GPs admitted 12,513 patients to the study between February 2004 and March 2007. The mean age was 64 years and 62% were males. Diabetes mellitus plus one or more cardiovascular risk factors was the main inclusion criterion (47%). About 30% of patients were included because of a history of atherosclerotic cardiovascular disease, 21% for four or more risk factors, and less than 1% for other reasons.

**Discussion:**

The Rischio and Prevenzione (R&P) project provides a feasible model to test the efficacy of n-3 polyunsaturated fatty acid therapy in patients at high cardiovascular risk with no history of myocardial infarction, and to assess how to implement recommended preventive strategies in general practice.

**Trial registration:**

ClinicalTrials.gov NCT00317707

## Background

Cardiovascular diseases (CVD) are the leading cause of death in middle-aged and older adults in most European countries. CVD are also an important cause of disability and morbidity and the main economic burden for health care services [1-4].

According to guidelines, patients with established CVD and those with multiple risk factors are at high cardiovascular (CV) risk and are therefore the main target for preventive strategies. These have to be tailored to the level of CV risk rather than aimed "only" at the treatment of individual cardiovascular risk factors [5]. Inadequate control of modifiable risk factors has been documented in various surveys [6-12] so there is considerable potential for improving cardiovascular prevention, especially in everyday clinical practice

While it is easy to see that general practice is a suitable setting for large-scale randomized controlled trials (RCTs) and prospective outcome-oriented studies [13-15], it is still rare to find general practice-based reports in the formulation and enforcement of guidelines for primary care physicians [16]. It is clear that until general practice itself is directly involved in research programs no significant or pertinent changes will ever be proposed and adopted.

Among possible preventive strategies, n-3 polyunsaturated fatty acids of marine origin (n-3 PUFA) are the newest and most promising. N-3 PUFA have been evaluated in pharmacological studies for their antithrombotic and anti-atherosclerotic effects, and their positive action on arrhythmias [17,18] has attracted a lot of attention.

After a pilot study to assess the feasibility of a large intervention study in the setting of general practice [10,19], the Rischio&Prevenzione (R&P) Study was launched in 2004. The project was designed to follow a cohort of patients at high CVD risk but with no history of myocardial infarction to test the efficacy of n-3 PUFA therapy, on the top of the other recommended preventive strategies (including lifestyle intervention and pharmacological treatments) aimed at optimizing the cardiovascular risk profile.

### Rationale of the n-3 PUFA hypothesis

The cardioprotective role of n-3 PUFAs, notably eicosapentaenoic acid (EPA) and docosahexanoic acid (DHA), referred to as omega-3 fatty acids or fish oil, is supported by substantial evidence. Most observational studies report an inverse relation between fish intake and coronary heart disease (CHD) mortality [20-24], especially sudden cardiac death [25-27]. This protective effect has been attributed to high EPA and DHA blood concentrations [25,28].

More direct evidence of the cardioprotective effect of omega-3 fatty acids comes from RCTs in patients with a history of myocardial infarction (MI). In 2033 post-MI men, a modest intake of fatty fish (200-400 g/week) or of n-3 PUFAs (0.5 g/day) reduced total mortality (primarily CHD deaths) by 29% during the two years of follow-up [29]. By far the largest trial was the GISSI Prevenzione study which tested the efficacy of 1 g/day of omega 3 fatty acids (as EPA and DHA) in 11323 patients with a recent MI (≤3 months) [17]. After 3.5 years, those receiving omega-3 fatty acids had a 20% lower relative risk of total mortality. Sudden death was the most affected cause, with 45% reduction, and the benefit appeared after only four months of therapy [18].

These results might be due to an antiharrythmic action of n-3 PUFAs and are in agreement with evidence from *in vitro *studies [30], animal models [31] and human studies [32].

The antiarrhythmic effect of n-3 PUFAs seems mainly to be due to electrical stabilization of cardiomyocytes, by increasing the electrical stimulus required to elicit an action potential and prolonging the relative refractory time. This might be through an action on sarcolemmal ionic channels: n-3 PUFAs inhibit fast voltage-dependent Na^+ ^currents, L-type calcium currents, and some potassium current components [33].

n-3 PUFAs may also exert beneficial effects through mechanisms such as antithrombotic, antiinflammatory, anti-atherogenic and triglyceride lowering actions, although these have been reported with higher doses than those needed to prevent arrhythmias in clinical settings (1 g/day n-3 PUFAs). These data underlie the American Heart Association recommendations that patients with CHD should consume 1 g/day of EPA+ DHA [34].

## Methods

### Study design and population

The R&P study is an ongoing large-scale, multicenter, randomized, double-blind, placebo-controlled clinical trial conducted in the setting of Italian general practice. The primary, experimental, aim of R&P is to assess the efficacy and safety of n-3 PUFAs in reducing cardiovascular mortality (including sudden death) and hospitalization for cardiovascular reasons in patients at high CVD risk but with no history of MI. The secondary, epidemiological, aim is to assess the feasibility of adopting current guidelines in everyday clinical practice in order to optimize all available preventive strategies in people at high cardiovascular risk (Figure 1).

**Figure 1 F1:**
[figure not shown]
**Rischio & Prevenzione study design**. n-3PUFA indicate polyunsaturated fatty acids.

Eligibility criteria were one of the following: 1) clinical evidence of atherosclerotic CVD such as angina pectoris, peripheral artery disease, previous ischemic stroke, transient ischemic attack or revascularization procedure; 2) multiple risk factors (at least four CV risk factors in non-diabetic patients and one or more in diabetics) including: old age (≥ 65 years), male sex, history of arterial hypertension, history of hypercholesterolemia, smoking, obesity (BMI ≥30 kg/m^2^), family history of premature CVD (<55 years in father or brother; <65 years in mother or sister); 3) other conditions putting the patient at high cardiovascular risk according to the general practitioner (GP)'s judgement.

The exclusion criteria were: prior MI, allergy to n-3 PUFAs, pregnancy, diseases with predictable poor short-term prognosis, and foreseeable psychological or logistic difficulties that would affect compliance with the project.

### Intervention strategies

Patients were randomly allocated to receive one capsule daily of 1 g n-3 PUFAs (850-882 mg EPA and DHA as ethyl esters with an average ratio of 1.0 to 1.2) or placebo (olive oil).

At the beginning and during the follow-up all patients were also evaluated and treated by their GPs according to current guidelines in order to optimize their CV risk management. At each visit GPs discussed with the patients their level of CV risk and the possible therapeutic strategies to be adopted or improved (e.g., control of blood pressure, glucose or cholesterol levels, weight reduction, stop smoking, increase physical activity, choose healthier foods, prescription of antiplatelets, etc.), and the therapeutic targets to be achieved in the next study period, completing an *ad hoc *check list.

### Study procedures

GPs were selected either through participation in previous research projects [16,35] or through the investigators' registries at local health units. GPs were invited to attend training meetings held with the patronage of local health units. During these meeting guidelines on cardiovascular prevention were presented and discussed.

Eligible patients were informed and gave their written consent to the study. Treatment was centrally allocated by telephone according to a computer-generated randomization list stratified by GP.

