### Statistical aspects

The primary endpoint at the start of the study was the cumulative rate of death plus non-fatal-MI and non-fatal stroke. The expected incidence of the primary endpoint was based on the literature and on the events observed in a subgroup of patients of a previous trial conducted in a similar setting of patients and GPs (16). Overall, the rate of events included in the primary endpoint was expected to be 2% per year (10% in five years). The goodness of these sample size calculation was to be assessed after one year of follow-up and the observed rate of events was in fact much lower than expected (1.4% instead of 2%).

Because n-3 PUFA seemed to have a positive influence on various CV outcomes besides the MI and stroke, and considering the increasing burden for public health systems of CV events requiring hospitalization, time to first occurrence of CV death and hospitalization for CV reason was then established as the primary efficacy endpoint of the trial. The expected cumulative rate of these combined end points during the five-year follow-up was assumed to be 15%. The minimum clinically relevant beneficial effect of the test treatment on the cumulative endpoint is set at 15% relative risk reduction (2.25% absolute risk reduction). Accordingly, to detect the efficacy of treatment with a power of 90% and α = 0.05 at least 11,202 patients must be included with a mean follow-up of five years and ≤10% drop outs. To guarantee adequate study power, an event-driven approach was adopted and patients will be followed-up until 1,383 events occur for the primary endpoint.

Statistical differences in the baseline characteristics of the treatment groups will be assessed with the χ^2 ^test for categorical variables and *t *test for continuous variables. Treatment efficacy on the primary endpoint, and on each single component, will be assessed using a Cox's proportional hazards' model [36], and the results will be expressed as hazard ratio (HR) estimates with 95% confidence intervals (CIs). Efficacy analyses will be adjusted for covariates found to be unbalanced between randomised treatments. Kaplan-Meyer estimates of the survival curves will be presented [37]. Time of occurrence of primary combined endpoint will be calculated according to the following hierarchy: time of occurrence of cardiovascular mortality or time of first occurrence of hospitalization for CV reasons.

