### Trial update

A total of 1,620 GPs attended 34 local training meetings organized throughout Italy; 860 (58%) out of 1486 GPs who initially agreed to join the study started to recruit patients (Figure 2). Between February 2004 and March 2007, 12,513 patients were enrolled. Each GP admitted an average of 14 patients (range 1-79); respectively 271 (31.5%), 564 (65.6%), and 25 (2.9%) GPs recruited ≤10, 11-20, and more than 20 patients.

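### Randomization is stratified by GP, but the published Cox analysis names no GP term and its covariate rule would not normally bring one in; a prespecified GP frailty is a cheap, minor improvement

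*Protocol article*

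**What the plan says.** - **Allocation** (Protocol article, Study procedures): "Treatment was centrally allocated by telephone according to a computer-generated randomization list stratified by GP".
- **Model** (Statistical aspects): efficacy on the primary endpoint and on each component "will be assessed using a Cox's proportional hazards' model", reported as hazard ratios with 95% confidence intervals.
- **Covariates** (Statistical aspects): "Efficacy analyses will be adjusted for covariates found to be unbalanced between randomised treatments". No other route into the model is described.
- **Endpoint** (Statistical aspects): "time to first occurrence of CV death and hospitalization for CV reason was then established as the primary efficacy endpoint of the trial".
- **Stratum size** (Trial update): 860 GPs in 57 local health units enrolled 12,513 patients. "Each GP admitted an average of 14 patients (range 1-79"; 271 GPs recruited 10 or fewer, 564 recruited 11 to 20, and 25 recruited more than 20.

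The article does not name GP as a stratum, random effect, cluster term or covariate. It also does not say that GP is excluded.

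**The concern.** The usual principle is to analyse by the factors used to randomize. Here the article does more than stay silent about GP. It gives a rule for covariates, and the rule works on observed imbalance. Allocation stratified by GP is meant to prevent imbalance on GP, so the one factor that the design controls is the one that the rule tends to leave out.

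GP could plausibly carry risk information. GPs deliver the background preventive treatment and follow patients in their own usual way (Intervention strategies; Data collection and follow-up), and the Discussion welcomes a varied population. Cardiovascular hospitalization, part of the primary endpoint, may also depend on local admission habits.

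Two things are at stake, both small. The first is a little precision already paid for by stratifying. The second is that unstratified, stratified and frailty models can give slightly different hazard ratios, so the choice is better fixed before unblinding.

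**Working it through.** **1. The plan's own figures.** Inputs from Statistical aspects: 15% in five years (taken as the control rate), "set at 15% relative risk reduction (2.25% absolute risk reduction" percentage points), hence 15% versus 12.75%; power 90%; α = 0.05 (two-sided reproduces the figure); up to 10% drop-outs.

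- Patients: the two-proportion formula with continuity correction gives 5,047 per arm. 2 × 5,047 = 10,094, and 10,094 / 0.9 = 11,216, against 11,202 stated. Without the correction, 9,918 / 0.9 = 11,020.
- Events: HR = ln(0.8725) / ln(0.85) = 0.839. Schoenfeld: 4 × (1.960 + 1.282)² / (ln 0.839)² gives 1,369; Freedman gives 1,376; 1,383 is stated. Power at 1,383 events is 90.3%.

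Neither calculation has a GP term, so nothing below changes these targets.

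**2. Sparseness.** 1,383 / 860 = 1.6 target events per GP.

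**3. Validity without a GP term.** Simulated trials used 860 GPs with sizes following Trial update, permuted blocks of four within GP (assumed) and log-normal GP effects with SD 0, 0.3, 0.5 and 0.8 (assumed), 1,000 trials each. Type I error of the unstratified Cox test was 4.2%, 4.3%, 4.9% and 3.9%. A second set with gamma frailty variance 0 to 0.6 (500 trials per setting) gave 3.8 to 5.4%. There is no inflation.

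**4. Attenuation.** At SD 0.8 with true HR 0.85, the mean log HR was −0.155 unstratified and −0.163 stratified by GP (true −0.163). 1 − 0.155/0.163 = about 5% towards zero, or HR 0.856 against 0.850.

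**5. Gain from a shared frailty.** Gamma frailty, true HR 0.84, 500 trials per setting. The change in effective events is the squared ratio of mean absolute Z.

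| Assumed frailty variance | Unstratified Z | Shared-frailty Z | Squared ratio |
|---|---|---|---|
| 0 | 3.33 | 3.33 | 1.00 |
| 0.3 | 3.30 | 3.36 | 1.04 |
| 0.6 | 3.23 | 3.35 | 1.08 (1.076) |

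**6. In power.**

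- Variance 0.3: Φ(3.30 − 1.96) = 91.0% and Φ(3.36 − 1.96) = 91.9%, a gain of 0.9 points.
- Variance 0.6: the same conversion gives Φ(1.27) = 89.8% and Φ(1.39) = 91.8%, or 2.0 points. This overstates the gain, because the unstratified statistic varies less than its model says. In step 4 the empirical SE was 0.0513 against a model SE of 0.0535, a ratio of 0.96. Borrowing that ratio, Φ(1.27 / 0.96) = 90.7%, so the gain is about 1.1 points.
- Direct check: 1,000 trials per setting, true HR 0.84, blocks of four, 15% control risk at five years, 10% drop-out, Weibull model with gamma frailty. Rejection was 90.1% unstratified and 90.8% with frailty at variance 0.3, and 90.1% and 91.3% at 0.6. The gains are 0.7 and 1.2 points.

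**7. Full stratification by GP.** With no GP variation, mean absolute Z fell from 3.33 to 3.30: (3.30/3.33)² = 0.98, about 2% fewer effective events. In the step 3 trials with a true HR of 0.85, power moved from 87.2% to 86.9% at SD 0 and from 83.4% to 84.1% at SD 0.8, within Monte Carlo error of about 1.1 points.

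**The case against.** **This is inference from silence in a condensed article.** The full protocol and analysis plan are not shown, and stratification terms are commonly left to them. A reader might infer that the trial will disregard GP; the article does not say so. This part of the objection stands, and it limits the point to what is published. It does not remove the point, because the article does state a covariate rule, and that rule would not normally select GP.

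**The planned analysis is not wrong.** A reader might infer that the unstratified confidence intervals or p-values are invalid. They are not. Randomization is of individuals within GP, so practice effects fall on both arms, and the test is at most slightly conservative. This stands in full.

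**The gain is small and rests on assumption.** No document gives between-GP variation, and at zero variation nothing is gained. Blinded central adjudication (Efficacy) limits differences between practices in how events are classified, though not in admission habits. This stands, and is why the point is minor.

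**The two models estimate different quantities.** Part of the shift in hazard ratio reflects the difference between a marginal hazard ratio and one conditional on practice. That is a choice of estimand, not the correction of an error. This also stands, and is a reason to state the choice beforehand.

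**Conclusion.** The point holds as a minor matter of specification. The published analysis names no term for the factor used to stratify randomization, and its only covariate rule would not normally supply one. The cost of leaving GP out is a slight attenuation relative to the within-practice hazard ratio and a slight loss of precision: nothing if practices do not differ, about 4% in effective events at frailty variance 0.3, 7 to 8% at 0.6, and about 1 point of power at the upper end. These sizes rest on the assumed frailty distribution and variance range, the assumed block size, and GP sizes drawn within the bands reported in Trial update.

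It would be too strong to conclude that stratified randomization obliges the trial to stratify the Cox model by GP. With about 1.6 target events per GP, that option widens standard errors and loses slightly when practices are alike. Nothing here calls the primary test, the 11,202 patients or the 1,383 events into question.

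**What to change.** In Statistical aspects (or the analysis plan, if it does not already say so), state that the primary Cox model includes GP as a shared frailty (random effect), independently of any observed imbalance, and that the unstratified Cox model is reported as a sensitivity analysis. Do not make a model stratified by all 860 GPs the primary one. If the full analysis plan already specifies how GP is handled, confirming this is enough.

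The cost is a sentence of wording and slightly more modelling. GP identity is already in the randomization list, so no new data are needed. The one change for readers is that the hazard ratio is then interpreted as conditional on practice, which the text should say.

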### Data collection and follow-up

Patients are followed by their GPs according to their usual practice, no additional instrumental/laboratory tests are required for the study. Data collection is scheduled annually, and follow-up is planned to last five years.

At enrolment, height, weight, waist circumference, heart rate and blood pressure were measured. History of CVD, risk factors and information on demographic factors, social status, lifestyle habits, laboratory tests and current medical therapies were collected. Patients were also required to complete a simple questionnaire about dietary habits, physical activity during leisure time, social life, psychological status and perceived CV risk level.

Clinical outcomes and adverse events are recorded when they advise and notified with an *ad hoc *clinical form.

Follow-up clinical visits include checking compliance and tolerance to the treatment. Updated information on any new diagnosis of CVD, control of risk factors, changes in lifestyle or dietary habits, and use of medications is also collected

All patients are to be followed up to the scheduled end of study, regardless of adherence to or discontinuation of the treatment for any reason. Study treatments are supplied according to the local health units' procedures.

### Efficacy

The main endpoint of the trial testing the efficacy of n-3 PUFA treatments is cardiovascular death or hospitalization for cardiovascular reasons. Secondary efficacy measures include: 1) the cumulative rate of death, non-fatal MI, non-fatal stroke; 2) the cumulative rate of cardiovascular death, non-fatal MI, non-fatal stroke; 3) coronary deaths; 4) sudden deaths. Additional analysis will be done on each component of the primary endpoint and in specific subgroups of patients corresponding to different risk levels or comorbidity. A specific evaluation is also planned of the benefit of the treatment on the reduction of fatal and non-fatal coronary and arrhythmic events. All outcome events are adjudicated by an *ad hoc *committee blind to the treatment allocation on the basis of pre-agreed definitions and procedures. All reports include a narrative summary and supporting documentation for every event (e.g. clinical records, death certificates and any other relevant documentation).

To assess the feasibility of optimizing cardiovascular prevention in the study population, the preventive strategies adopted and the goals chosen at the outset and during follow-up will be analyzed, as well as their efficacy in terms of risk factor control and therapeutic targets attained.

### Safety

All serious adverse events (defined as fatal, life-threatening, requiring or prolonging hospitalization, permanently disabling or incapacitating, which may jeopardize the subject or which may require medical or surgical intervention), not necessarily drug-related, are reported on a standard form and communicated to the study Coordinating Center within 24 hour of notification of their occurrence. Safety is monitored by an external Data Safety Monitoring Board (DSMB).

